#### Resistance training

Participants will complete 8-weeks of supervised progressive resistance training twice per week on non-consecutive days at Deakin University Burwood campus. The sessions will be supervised by a qualified exercise trainer (e.g., exercise physiologist or qualified strength and conditioning coach) to monitor correct lifting and rest intervals. Each resistance training session (45 to 60 min in duration) will consist of eight exercises completed as four complex pairs. The exercises and complex pairs include: 1A leg press + 1B countermovement jump, 2A bench press + 2B bench press throw, 3A deadlift + 3B deadlift jumps, and 4A bench pull + 4B power bench pull. The strength-focused exercises (denoted with letter “A” of each complex pair) will be performed with a slow and controlled eccentric phase of ~ 2–3 s for increasing time under tension (stimulus for hypertrophy) and an explosive concentric phase (stimulus for strength and power development) with higher loads. The power-focused exercises (denoted with letter “B” of each complex pair) will be performed explosively (I.e., as fast as possible) in the eccentric and concentric phases with lower loads. The loads prescribed for the strength- and power-focused exercises will be calculated as percentages of the 1-RM either assessed directly (bench press) or predicted from a 6-RM (leg press, bench pull and deadlift) as determined in the familiarisation week**.** During weeks 3–8, an extra set will be performed for each of the strength-focused exercises whereby the load will be decreased (to 50 - 60% 1-RM) and participants will perform as many reps as possible (AMRAP). Some additional accessory exercises (e.g., leg curls, biceps curls and triceps pushdowns) to achieve muscle balance will also be added at this time. Rest between sets and exercises will range from 3–5 min. The prescription of the repetitions, sets and loads are outlined in Table 1.

**Table 1 Tab1:** Repetition, sets and loads to be used during the 8-week progressive resistance training program

	**Sets**	**Repetitions**	**Load** **(Strength exercises)**	**Load** **(Power exercises)**
Weeks 1–2	3	6	75% 1RM	45% 1RM
Weeks 3–4	3	5 AMRAP	80% 1RM 50-60%	50% 1RM
Weeks 5–6	4	4 AMRAP	85% 1RM 50-60%	55% 1RM
Weeks 7–8	5	3 AMRAP	90% 1RM 50-60%	60% 1RM

*AMRAP* as many reps as possible

Following each resistance training session, participants will be provided with a flavoured whey protein concentrate beverage (250 Cals; 40 g protein) mixed with 200–300 ml of water to be consumed within 15 min of completing the session to support and maximise muscle protein synthesis and promote muscle hypertrophy adaptations.

#### Study outcomes

For all testing visits, participants will be required to arrive in a fasted state and to avoid any strenuous exercise in the 24-h prior to testing. The schedule of enrolment, interventions and assessments  is outlined in Fig. 1.

**Fig. 1 Fig1:**
[figure not shown]
Schedule of enrolment, interventions and assessments

### Primary outcomes

#### Lean body mass

The primary outcomes will be the mean (± standard deviation, SD) difference between the two groups for total body (%) (DXA; Lunar Corp., Madison, WI) and regional (e.g., mid-thigh) lean muscle mass (%). Regional muscle mass will be assessed by the measurement of the mid-thigh cross sectional area (cm^2^) which will be measured by a Perpheral Quantitative Computered Tomography (pQCT;XCT 3000, Stratec Medizintechnik GmbH, Pforzheim, Germany). A tomographic slice will be taken 66% proximal from the distal tibia on the right leg, which is considered the largest cross-sectional area of the lower leg [36]. The pQCT results will be analysed using the BoneJ plugin for ImageJ [37]. Measurements for the DXA and pQCT will be taken at familiarisation (week 0), pre-testing (week 1) and post-testing (week 11) and all scans will be carried out by the same researcher (ZH). The outcomes taken over the two consecutive weeks (e.g., familiarisation and baseline) will allow for researchers to report the coefficient of variation (CV) values to report test-retest reliability. For both the pre-testing and post-testing visits participants will be asked to consume 500 ml of water 45–60 min prior to body composition testing to control for hydration status and to minimise the influence hydration status on DXA- derived measure. Confirmation of hydration status will also be carried out via measuring plasma osmolality (Osmomat 3000, Gonotec, Utah, United States of America) from plasma taken from venous blood samples in duplicate.

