**Methods:**

This double-blind, randomised controlled study will take place over an 11-week period (including 8-weeks of progressive resistance training). Participants for this study will be 18–35 years old, healthy active adults that are not resistance trained. Participants will attend a familiarisation (week 0), pre-testing (week 1) and final-testing (week 11). At the pre-testing and final-testing weeks, total lean body mass (dual-energy X-ray absorptiometry; DXA), total mid-thigh cross sectional area (pQCT), maximal muscular strength (1 repetition maximum bench press, isometric mid-thigh pull) and power (countermovement jump and bench throw) will be assessed. Additionally, circulating inflammatory cytokines and anabolic hormones, sleep quality and quantity (ActiGraph), pain and subjective wellbeing (questionnaires) will also be examined.

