### Objectives

The primary aim of this study is to investigate the effects of daily PEA supplementation (Levagen + ®) during an 8-week period of resistance training on pre- to post-intervention changes in total body and regional lean body mass (e.g., mid-thigh) compared with a placebo condition. Our secondary aims are to explore the effects of PEA supplementation on changes in strength, power, sleep, subjective wellbeing, and pain associated with resistance training and menstruation.

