### Sample size

It has been calculated that a sample size of 42 participants (21 per group) will provide 80% power, for α = 0.05, to detect a 2% difference between groups in percentage lean mass change [assumed SD = 2.2% based on data from [42] to detect a significant change in lean muscle mass. To allow for an ~ 20% dropout rate, we will aim to recruit 52 participants in total. As proof of principle, a study by Lilja et al. [19] demonstrated a significant difference in muscle mass and strength between participants treated with NSAIDs vs placebo after 8 weeks of resistance training with a participant pool of 35 participants. Sample size calculations were performed in Stata/SE 16.1 (StataCorp, TX) using the *power two means* command.

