## Discussion

For athletes, pain management either from injury or associated with training and exercise can influence athletes' immediate or future performances. Athletes have unrestricted access to over-the-counter pain management such as NSAIDs and other analgesic medications, and reports have indicated prolonged prophylactic use by some athletes [14–19]. Athletes that regularly take NSAIDs and other analgesics medications may be at risk of lower muscular adaptations due to the inhibitory effects these medications may have on intramuscular pathways such as the cyclooxygenase-2 (COX-2) [19–22]. The aim of this study is to explore an alternative option to pain management for athletes and to investigate the effects of daily PEA supplementation (Levagen + ®) on pre- to post-intervention changes in total body and regional lean body mass and mid-thigh cross-sectional area compared with a placebo condition during an 8-week period of resistance training. Our secondary aims are to explore the effects of PEA supplementation on changes in strength, power, sleep, subjective wellbeing, and pain associated with resistance training and menstruation. This study is the first of its kind to evaluate the effectiveness of PEA supplementation in the context of skeletal muscle hypertrophy to be applied to an active population.

The results of this study may assist active individuals, athletes and their coaches in making an informed decision about the most appropriate pain management strategy for them. If PEA is found not interfere with, or to enhance training induced muscle hypertrophy and improve sleep, then it may be a better pain relief option than OTC medications. These findings may be beneficial for those that work with and manage athletes such as sports physicians, coaches, strength and conditioning coaches and the athletes themselves. The findings from these studies will be presented at meetings, conferences and published in peer-reviewed scientific journals.

A potential limitation of this study is the exclusion of participants with experience in structured resistance training in the past 12-months. This may limit the generalisation of our findings to non-strength trained populations.

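### The regional primary outcome is named as lean muscle but measured as a mid-thigh area of unstated tissue (called total in the abstract), so as written it cannot separate muscle change from fat change

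*Protocol article*

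**What the plan says.** The Objectives set the primary aim as "changes in total body and regional lean body mass (e.g., mid-thigh) compared with a placebo condition". The Lean body mass section names the second primary outcome as "regional (e.g., mid-thigh) lean muscle mass", with per cent as the unit. The next sentence gives the measure: "Regional muscle mass will be assessed by the measurement of the mid-thigh cross sectional area", in cm², by pQCT. For image processing it says only this: "The pQCT results will be analysed using the BoneJ plugin for ImageJ". The tissue to be extracted is not named.

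The abstract describes the same measure as "total mid-thigh cross sectional area (pQCT". The Discussion gives the aim as changes in "total body and regional lean body mass and mid-thigh cross-sectional area compared with a placebo condition", which lists the area next to regional lean mass.

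The Lean body mass section also fixes the scan position: "A tomographic slice will be taken 66% proximal from the distal tibia on the right leg". That is a lower-leg site, although the outcome is called mid-thigh.

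**The concern.** A limb cross-section contains muscle, fat and bone. The aim concerns lean tissue, while the measure is an area with no tissue named, and its only qualifier anywhere in the article is *total*. The unit also moves from per cent to cm² without a stated conversion.

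An analyst who followed the text literally would test whole-limb area as a primary outcome. A participant who gained muscle and lost fat could show no change, and one who gained only fat would count as having grown muscle. Both sexes are enrolled across a BMI range of 18.5 to 28 and keep their own usual diet, so some individual change in fat area is plausible. If the compartment is left open, the choice between total and muscle area could also be made after the results are seen.

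**Working it through.** **1. The wording, side by side**

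| Place | What is named | Tissue | Unit |
|---|---|---|---|
| Objectives | regional lean body mass | lean | none |
| Lean body mass, outcome | regional lean muscle mass | muscle | % |
| Lean body mass, measure | mid-thigh area by pQCT | none | cm² |
| Abstract, Methods | total mid-thigh area by pQCT | called total | none |
| Discussion | regional lean mass and mid-thigh area | none for the area | none |

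No row names muscle area or removes fat and bone.

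**2. The plan's own sample size**

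Inputs from Sample size and Statistical methods: difference 2%, SD 2.2%, two-sided α = 0.05, 80% power, 21 per arm. For a two-sample t-test the noncentrality is δ / (σ√(2/n)) = 2 / (2.2 × √(2/21)) = 2.95 on 40 degrees of freedom. This gives 82.0% power. With 20 per arm, power is 79.997%, just under target, so 21 per arm (42 in total) reproduces. For dropout, 42 / 0.8 = 52.5 against the stated 52, which agrees within rounding. The calculation is built on percentage lean mass change and does not depend on how the regional area is defined.

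**3. What a total area does to a muscle effect**

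Total area is T = M + F + B (muscle, fat, bone). In relative terms, with bone unchanged:

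%ΔT = m × %ΔM + f × %ΔF

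where m and f are the muscle and fat shares. These shares are not in the documents. I assume m = 0.6 to 0.8, bone 0.03 and f = 0.97 − m. I also borrow the plan's 2% and 2.2% for muscle area, which the plan does not do.

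*(a) Fat and bone do not change.* In cm², ΔT = ΔM and nothing is lost. On the relative scale the effect becomes 2m and the SD 2.2m. Their ratio is unchanged, so power stays at 82%.

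*(b) Fat area varies between participants, independently of muscle and equally in both arms.* The SD of %ΔT is √[(2.2m)² + (f × s)²], where s is the SD of fat-area change, assumed to be 3%, 6% or 10%. For m = 0.6 and s = 3: √(1.32² + 1.11²) = 1.72. Power with 21 per arm:

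| m | Difference in total area | s = 3% | s = 6% | s = 10% |
|---|---|---|---|---|
| 0.6 | 1.2% | SD 1.72, 60% | SD 2.58, 31% | SD 3.93, 16% |
| 0.7 | 1.4% | SD 1.74, 72% | SD 2.24, 51% | SD 3.11, 30% |
| 0.8 | 1.6% | SD 1.83, 79% | SD 2.03, 70% | SD 2.45, 54% |

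*(c) One participant.* With m = 0.6 and f = 0.37, a 2% muscle gain adds 1.2% to total area. A fall in fat area of 1.2 / 0.37 = 3.2% cancels it. A 3.2% rise in fat area with no muscle change looks the same as a 2% muscle gain.

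*(d) Reversal between groups.* The difference in total area changes sign only if fat-area change in the PEA arm is lower than in the placebo arm by more than 2m / f: 1.2 / 0.37 = 3.2, 1.4 / 0.27 = 5.2 or 1.6 / 0.17 = 9.4 percentage points.

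**The case against.** The strongest reply is that the article states the purpose plainly. The outcome is called lean muscle mass, the area is there to assess muscle, and the scans go through image-analysis software. *Total* appears only in the abstract and may be loose wording. Segmentation settings commonly sit in a full protocol or analysis plan that is not shown, so their absence from an article is no fault. Whole-body lean mass by DXA is also a primary outcome, so the lean-mass aim does not rest on this measure alone.

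Much of this stands. The documents do not prove that fat and bone will be counted, and density thresholds cannot be demanded of an article. But the article does state the measured quantity. It never calls that quantity muscle area, and where it qualifies it the word points the other way. If segmentation is intended, one sentence settles the matter. If it is not, a primary outcome does not measure its objective.

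Two stronger readings are tempting. A reader might infer that a total area automatically dilutes the effect by the non-muscle share. It does not: step 3(a) shows no loss in cm² and no loss of power in relative terms when fat and bone are stable. Only added fat-area variance costs power. A reader might also infer that a real muscle gain could come out reversed. For the group comparison this needs a PEA-specific effect on fat, which the protocol nowhere hypothesises. Both arms receive the same training and the same request to keep their usual diet, and fat loss common to both arms drops out of the comparison.

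**Conclusion.** The concern holds as a mismatch between a named concept (lean muscle, per cent) and a stated measure (an area of unspecified tissue in cm², called total in the abstract). As written, the regional primary outcome cannot separate muscle change from fat change. Fat change can therefore obscure a muscle effect or pass for hypertrophy.

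The size is not derivable from the documents. The 16% to 79% range in step 3(b) rests on assumed tissue shares, an assumed SD of fat-area change, independence of muscle and fat change, and the whole-body effect and SD borrowed for a regional area. It uses a simple t-test rather than the planned baseline-adjusted model. The shares were chosen with a thigh in mind and would need revisiting for a lower-leg slice. With no fat variation the loss is nil.

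Neither automatic dilution nor a reversed group difference is supported, and the stated sample size stands. The correction should be made before unblinding.

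**What to change.** In the abstract's Methods, the Lean body mass section and the Discussion, use one definition of the regional primary outcome: pQCT muscle cross-sectional area, excluding fat and bone, in one stated unit (change in cm² or per cent change). State that muscle is segmented in the image-analysis software already named, under a rule fixed before unblinding. Report total and fat area as descriptive outcomes only.

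In the same edit, reconcile the mid-thigh label with the tibial slice position, so that the tissue and the site describe the same scan.

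The cost is a wording change plus segmentation work, with no extra visit and no extra radiation. Assessors are to stay blinded until after the analysis, so images already taken can be re-read without bias. They can yield muscle area only at the site actually scanned: if slices were taken on the lower leg, re-reading will not give a mid-thigh measure. The sponsor should also confirm that the named software supports the separation, which the article does not say.

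### As written, the pQCT slice site (tibia, lower leg) contradicts the named regional primary outcome (mid-thigh)

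*Protocol article*

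**What the plan says.** Under Lean body mass, the Protocol article lists two primary measures: total-body lean mass by DXA and "regional (e.g., mid-thigh) lean muscle mass". For the second it states: "Regional muscle mass will be assessed by the measurement of the mid-thigh cross sectional area", in cm², by pQCT. The next sentence fixes where the scan is taken: "A tomographic slice will be taken 66% proximal from the distal tibia on the right leg", and adds of that site "which is considered the largest cross-sectional area of the lower leg". DXA and pQCT are both scheduled at week 0 (familiarisation), week 1 (pre-testing) and week 11 (post-testing), and the first two visits supply the test-retest coefficient of variation.

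The mid-thigh is also named in three other places:

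- Abstract, Methods: "total mid-thigh cross sectional area (pQCT".
- Objectives: "total body and regional lean body mass (e.g., mid-thigh) compared with a placebo condition".
- Discussion: "total body and regional lean body mass and mid-thigh cross-sectional area compared with a placebo condition".

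**The concern.** The tibia is a bone of the lower leg, and the article says as much about the slice site. A slice there shows calf muscle and cannot pass through the thigh. The outcome name and the acquisition instruction therefore describe two different body parts, in adjacent sentences, for a primary outcome.

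If the instruction is what is carried out, a lower-leg result will be published as a mid-thigh result, and the test-retest figure will carry the same wrong label. If the outcome name is what is carried out, the published acquisition method is wrong and nobody could repeat the measurement from it. In both cases a reader could not tell which muscle a positive or null regional finding refers to. If the question is settled only after results are known by group, the correction could look like a post hoc change to a primary outcome.

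**Working it through.** No arithmetic decides this point. It rests on setting the statements side by side.

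| Place in the Protocol article | Site named |
|---|---|
| Abstract, Methods | mid-thigh, by pQCT |
| Objectives | mid-thigh, as the example of regional lean mass |
| Lean body mass, outcome sentence | mid-thigh, as the example of regional lean muscle |
| Lean body mass, measurement sentence | mid-thigh cross-sectional area, by pQCT |
| Lean body mass, acquisition sentence | 66% site on the tibia, described as lower leg |
| Discussion | mid-thigh cross-sectional area |

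1. *Is a second slice described?* No. The acquisition sentence refers to a single slice, and no section gives a femoral or thigh landmark.
2. *Is a lower-leg outcome named anywhere?* No. The tibial slice has no outcome of its own to serve, so it can only be meant as the measurement of the regional outcome.
3. *Could the tibial landmark still describe a thigh site?* No. The same sentence rules that out by placing it in the lower leg.
4. *Does the loose wording of the region remove the conflict?* The Objectives and the outcome sentence give the mid-thigh only as an example. The measurement sentence and the Abstract, however, tie pQCT specifically to the mid-thigh, so the conflict stays.

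**Does it touch the sample size?** The Sample size section states that "a sample size of 42 participants (21 per group) will provide 80% power, for α = 0.05", for a 2% difference in percentage lean mass change with SD 2.2%. Reproducing this with a two-sample t-test, two-sided:

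- Standardised difference: 2 / 2.2 = 0.909.
- Required n per group for 80% power: 20.002, rounded up to 21, so 2 × 21 = 42. This matches the stated figure.
- Power at 21 per group: 82.0%. At 20 per group: 79.997%, just short.
- Dropout: 42 / (1 − 0.20) = 52.5. The stated 52 implies 1 − 42/52 = 19.2%, consistent with a dropout given as approximately 20%.

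The inputs are a difference and an SD for percentage lean mass change. No pQCT area enters the calculation, so correcting the scan site or the outcome name leaves 42 and 52 unchanged.

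**The case against.** The strongest reply is that this is a slip in one sentence. The mid-thigh is named in four sections and the tibial landmark appears once, with a supporting citation that is not available here. The thigh may have been scanned throughout. That is possible, and the text cannot exclude it. What stands is that a reader cannot tell. A count of mentions does not settle the matter either, because the single tibial sentence is the only one that tells an operator where to scan.

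A second reply is that a journal article leaves scanning detail to the full protocol. That would excuse an omission. Here the article does state a site, and the site conflicts with the outcome.

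A reader might go further than the documents allow in four ways:

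- *All pQCT data are invalid.* This assumes the tibial sentence is what was done, which the article does not show.
- *The lower leg would respond least to this programme.* Nothing in the article ranks muscle groups by response. The Resistance training section prescribes leg press, countermovement jumps and deadlift jumps, which isolate neither segment.
- *Total area, including fat and bone, will be analysed instead of muscle.* This rests on one adjective in the Abstract. The outcome section speaks of muscle, and the word may mean total muscle area.
- *The pQCT outcome must become secondary, or be replaced by a DXA regional measure.* The contradiction does not require this. A correctly named lower-leg area could still serve a regional aim for which the thigh is only an example, and exchanging a primary outcome during the trial raises concerns of its own.

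**Conclusion.** The point holds as an internal contradiction in the definition of a primary outcome. One of the two primary measures has a named site and a scanned site that cannot both be right, and the conflict applies to every pQCT visit (weeks 0, 1 and 11) if the instruction is followed. The supportable harm is mislabelling: lower-leg area reported as mid-thigh muscle. Whether that has happened depends on the site actually scanned, which the article does not reveal.

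The DXA total-body primary outcome and the sample size are unaffected. Because the contradiction concerns what a primary outcome measures, it must be corrected and is more than a clerical matter.

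**What to change.** Before unblinding, check the stored pQCT scans and state the site actually acquired: limb segment, anatomical landmark and the reference length to which the percentage applies. Then make one of two corrections.

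- **If the scans are at the tibial site:** rename the outcome lower-leg muscle cross-sectional area (cm²) in the Abstract, Objectives, Lean body mass and Discussion sections, and stop describing it as mid-thigh.
- **If the scans are at the mid-thigh:** replace the tibial landmark and the lower-leg description under Lean body mass with the thigh landmark used. The outcome name then stands.

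In either case, keep the site the same at weeks 0, 1 and 11, so that the change score and the test-retest figure refer to the same location, and date the correction so that it is seen to precede unblinding.

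The cost is a check of existing scans and a wording correction to the protocol and, where it names the site, the registry entry (not available for this review). No new scans and no change to the sample size are needed. The Allocation concealment and blinding section keeps allocation from the data-collection team until after analysis, and Trial status reports recruitment still ongoing, so on the published timetable the correction could be made blinded.
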